## Abstract

**Background:**

Pregnancy is a complex time characterized by major transformations in a woman, which impact her physical, mental, and social well-being. How a woman adapts to these changes can affect her quality of life and psychological well-being. The literature indicates that pregnant women commonly experience psychological symptoms, with anxiety, stress, and depression being among the most frequent. Hence, promoting a healthy lifestyle focused on women’s psychological well-being is crucial. Recently developed digital solutions have assumed a crucial role in supporting psychological well-being in physiologically pregnant women. Therefore, the need becomes evident for the development and implementation of digital solutions, such as a virtual coach implemented in a smartphone, as a support for the psychological well-being of pregnant women who do not present psychological and psychiatric disorders.

**Objective:**

This study aims to assess the feasibility, acceptability, and utility of a mindfulness-based mobile app. The primary objective is to explore the feasibility of using a virtual coach, Maia, developed within the TreC Mamma app to promote women’s psychological well-being during pregnancy through a psychoeducational module based on mindfulness. Finally, through the delivery of this module, the level of psychological well-being will be explored as a secondary objective.

**Methods:**

This is a proof-of-concept study in which a small sample (N=50) is sufficient to achieve the intended purposes. Recruitment will occur within the group of pregnant women belonging to the pregnancy care services of the Trento Azienda Provinciale per i Servizi Sanitari di Trento. The convenience sampling method will be used. Maia will interact with the participating women for 8 weeks, starting from weeks 24 and 26 of pregnancy. Specifically, there will be 2 sessions per week, which the woman can choose, to allow more flexibility toward her needs.

**Results:**

The psychoeducational pathway is expected to lead to significant results in terms of usability and engagement in women’s interactions with Maia. Furthermore, it is anticipated that there will be improvements in psychological well-being and overall quality of life. The analysis of the data collected in this study will be mainly descriptive, orientated toward assessing the achievement of the study objectives.

**Conclusions:**

Literature has shown that women preferred web-based support during the perinatal period, suggesting that implementing digital interventions can overcome barriers to social stigma and asking for help. Maia can be a valuable resource for regular psychoeducational support for women during pregnancy.

**International Registered Report Identifier (IRRID):**

RR1-10.2196/53890

## Introduction

### Overview

The transition to motherhood represents a profound shift in a woman’s life, necessitating a reorganization of her identity, skills, attitudes, and values [1]. Pregnancy is characterized by major transformations. Pregnancy brings about substantial changes that impact a woman’s physical, mental, and social well-being. How a woman adapts to these changes can affect her quality of life (QoL) and psychological well-being. The literature indicates that pregnant women commonly experience psychological symptoms, with anxiety, stress, and depression being among the most frequent. Specifically, between 12.2% and 39% of pregnant women are reported to experience symptoms of anxiety and psychosocial stress [2], the latter defined as “an imbalance that a pregnant woman perceives when she is unable to cope with the demands of the new condition, which manifests itself behaviourally and psychologically” [3]. These findings were also confirmed by the study conducted by Woods et al [4], which revealed that 6% of women reported high levels of stress symptoms, 78% exhibited low to medium stress symptoms, and 16% reported no stress symptoms. Other studies have investigated perinatal depression in pregnant women, which has been recognized as a prevalent clinical condition [5]. Specifically, the study [5] found an incidence of depressive symptoms reaching 14.5% during pregnancy and 49% during the first year after delivery. Therefore, both pregnancy and the transition to motherhood are commonly seen as vulnerable periods marked by escalating worries and fears about managing the changes ahead, including caring for the baby or children yet to be born [6]. Therefore, it is crucial that pregnancy is experienced positively by women, thereby fostering the development—spontaneous or voluntary—of a positive level of cognitive motivation [7]. Indeed, promoting a healthy lifestyle focused on the woman’s psychological well-being is central to her mental health and future relationship with the child or children.

To date, psychoeducational interventions promoting women’s psychological well-being during pregnancy are scarce. They tend to focus on the effect of such interventions on specific subgroups of pregnant women with psychiatric symptoms (eg, perinatal depression disorder). Using digital tools to promote psychological well-being can be optimal for pregnant women, who can benefit from the intervention by accessing them anywhere and at any time. In addition, digital interventions are designed to be flexible to the mother’s needs and reduce the barriers related to social stigma and help-seeking behaviors [8,9]. Therefore, promoting tailored and easily accessible digital interventions aimed at addressing the specific needs of mothers during the transitional period is crucial for fostering positive relationships with their children. In this regard, a growing body of evidence reports promising results concerning the effectiveness of evidence-based mindfulness interventions delivered via web for promoting the psychological well-being of pregnant women [10,11]. Studies have also found that the psychological state of the pregnant woman appears to be closely related to the course of the pregnancy and the psychological and cognitive development of the child. Indeed, the literature reports a positive association among anxiety, stress symptoms, the likelihood of preterm delivery, and the variability in fetal heart rate [12]. Therefore, mindfulness interventions provide an active approach to managing stress levels, anxiety symptoms, and depression, aiming to reduce them. Thus, developing skills related to this practice enables women to mindfully deal with many potentially critical situations, including the moment of childbirth.

In conclusion, the psychoeducational interventions heralded through the use of digital solutions reported so far are shown to be a viable solution with the potential to promote psychological well-being, support the psychological adaptation of women in physiological pregnancy, and prevent the development of clinically relevant symptoms.

### Local Background

The autonomous province of Trento (PAT) is committed to promoting community welfare by providing a comprehensive initiative supporting and empowering parents at the provincial level. This includes a wide range of preventive, protective, and curative interventions spanning from early pregnancy to the first thousand days of a child’s life. These interventions are designed to have significant short-, medium-, and long-term health impacts for the newborn in both childhood and adulthood as well as for parents, the community, and future generations. In these initiatives, the integration of digital health tools is a crucial component within the framework of a pervasive digital health approach [13].

The overall strategy to support pregnant women begins with the active provision of the Birth Pathway initiative. The Birth Pathway encompasses all services aimed at promoting the health of women, infants or newborns, and families, providing appropriate care throughout pregnancy, childbirth, and postpartum, including support during breastfeeding, the postpartum period, and parenting.

Because of these comprehensive efforts at the provincial level, in 2022, the PAT and the provincial health services institution (Azienda Provinciale per i Servizi Sanitari—Azienda Provinciale per i Servizi Sanitari di Trento; APSS) achieved the United Nations International Children's Emergency Fund—Baby Friendly Initiatives accreditation for all birthing facilities and the community. This accreditation reflects the long-lasting commitment to the continuous improvement of care standards and outcomes. The PAT is also designated as Friends of Children, a status which the Trento birthing facility had already attained in 2015.

This research project has been developed in full harmonization with the overall principles of the PAT initiatives mentioned in the previous paragraphs and considering the broader provincial context in terms of organizational assets and service delivery. In particular, the project is promoted in the context of the First Thousand Days Module scenario of the Digital health care and artificial intelligence—tools for bringing the health service closer to citizens and for the development of the provincial system project, described and approved in deliberation number 2475 of the PAT on December 22, 2022. This strategy scenario is geared toward enhancing well-being and promoting healthy lifestyles during normal pregnancies, while also incorporating digital health principles and tools into organizational assets.

### Goal of the Study and Research Questions

This study is positioned within the design and development cycle of the Obesity-Related Behavioral Intervention Trials model (specifically the Refine phase) [14]. It involves delivering mindfulness-based materials in text, audio, and video formats by a virtual coach (ie, a digital assistant, hereafter identified as Maia) implemented within the TreC Mamma app.

This intervention is positioned within the framework of behavior change interventions [15], which aim to enable women to acquire adaptive strategies for their psychological well-being. It is emphasized that the term intervention in this context is used to identify an app (in this case, the virtual coach) that will periodically offer, in a predefined (ie, rule based), structured, and ordered manner, informational materials in audio, text, and video formats, which will be structured and reviewed by psychological professionals.

The end user reads and manages this material independently; therefore, the virtual coach will be used as a simple information transmission tool. In addition, the software (app and virtual coach) is used to administer questionnaires and collect, store, and transmit data in this project. This intervention has been developed and implemented for research purposes, with the final goal of validating a digital health intervention targeting women’s psychological well-being during pregnancy through a module of mindfulness practices.

### Primary Objectives

The primary objectives of this proof-of-concept study are (1) to exploratively investigate user experience (UX) and user engagement (UE), that is, women’s experience and engagement with the TreC Mamma app and the virtual coach dedicated to the mindfulness intervention (Maia); and (2) to assess the women’s UE with Maia and the TreC-Mamma app through semistructured interviews and investigate their feelings and overall experience during the psychoeducational intervention.

### Secondary Objective

The secondary objective is to assess the level of pre-post psychological well-being through administering self-report questionnaires at the beginning and the end of the intervention.

### Maia Intervention

The virtual coach, Maia, is structured to deliver a module featuring psychoeducational content based on mindfulness to promote the QoL and psychological well-being perceived by pregnant women. The module is self-administered and available on both Android and iOS devices. All the contents of the dialogues have been developed by a group of researchers from the Digital Health Research of the Bruno Kessler Foundation (Fondazione Bruno Kessler–Trento; FBK) of Trento and psychologists from the Istituto Pavoniano Artigianelli with specific skills in mindfulness protocols and communication. Subsequently, materials have been revised by a psychologist from the psychology operating unit of the APSS of Trento. The dialogues, videos, and audio tracks were developed based on an educational rather than an emergency management approach.

### Technological Tools

The technological component of the study is based on TreC Mamma. This platform allows citizens of the PAT to access, manage, and share information regarding their health and well-being [16]. TreC stands for *cartella clinica del cittadino* and is a reliable and well-tested platform designed to be a “system of systems” rather than a simple data hub. The central pillar of the TreC Mamma platform is the role of the citizen or patient as the manager of their own health-related data as in the case of a personal health record. TreC Mamma is designed with a flexible architecture, which enables the collection and management of heterogeneous data and allows the development and use of further subsystems to provide additional and specific functions.

This research project uses an additional module of the TreC Mamma platform, called TreC Mamma, a technological platform for supporting pregnant women who are residents in the PAT and are enrolled to APSS’s services. TreC Mamma can be downloaded for free by all pregnant women in the provincial health service. Authentication should be carried out via the *sistema pubblico di identità digitale* (ie, the public digital identity system) or *carta di identità elettronica* (ie, electronic identity card), which are secure national identification system services.

### Mindfulness Practices Module

The mindfulness practice intervention lasts 8 weeks, with 2 sessions of approximately 10 minutes each per week. Figure 1 shows a graphical representation of the conversational protocol delivered to women and its chronological structure.

**Figure 1 figure1:**
[figure not shown]
Graphical representation of the conversational protocol delivered to the participants and its chronological structure. DASS-2: Depression Anxiety Stress Scales–21; ERQ: Emotion Regulation Questionnaire; FFMQ: Five Facet Mindfulness Questionnaire; IES-R: Impact Event Scale–Revised; MARS: Mobile Application Rating Scale; PANAS-SF: Positive and Negative Affect Schedule–Short Form; SF-12v1: Short Form–12 Health Survey Version; UES-SF: User Engagement Scale–Short Form; UX: user experience.

This module aims to enable women to acquire healthy coping strategies with specific reference to mindfulness practices to promote psychological well-being during and after pregnancy. Pregnant women can learn mindfulness techniques to manage the typical anxiety and stress experienced during pregnancy, cope with pain and fear during childbirth, and enhance couple cooperation and parental sensitivity.

The module was developed in line with the mindfulness-based childbirth and parenting approach [17], adapting it to a psychoeducational intervention delivered via a virtual coach. The contents are presented through a gradual pathway that will enable the woman to be mindful of herself and the present moment, to accept and normalize internal states, to cope with stress, and to perceive an improvement in her psychological well-being. Specifically, formal practices (eg, “body scan”) and informal practices (eg, audio tracks on “eating a meal with mindfulness”), readings, or videos related to important topics about mindfulness practice will be proposed. Furthermore, the woman will be asked to carry out tasks independently. If she wishes, she can ask for support from her partner or a trusted person for some practices, but it is not mandatory.

## Methods

### Design and Study Plan

Maia is designed to interact with pregnant women 8 weeks from the 24th and 26th week of pregnancy. Precisely, 2 sessions per week are planned. The woman can choose the day and time that best suits her needs to interact with Maia.

At the beginning of the psychoeducational pathway, Maia will administer 6 self-report questionnaires, described in the Data Collection section, to establish a baseline.

After the data collection phase, the psychoeducational module will be administered, and its contents will be presented in different formats (ie, text, images, audio tracks, and video tracks).

An additional round of administering questionnaires is expected at the end of the psychoeducational intervention to assess potential changes in terms of the psychological well-being and QoL perceived by the women. Two questionnaires will be administered to assess usability. Reminders will be scheduled to fill out the questionnaires 24, 48, and 72 hours after the first request to ensure the collection of all the necessary data. However, at present, there are no reminders for session completion.

Two months after giving birth, women who have given their consent will be invited to a semistructured interview to investigate their experience of using Maia and the TreC Mamma app and to collect a more in-depth understanding of their experiences during the psychoeducational process. The 2-month postpartum period was chosen for both organizational convenience and methodological considerations. The expert group identified this timeframe to find a balance between scientific appropriateness and practical arrangements of the interviews, avoiding a prolonged span after the end of the intervention while ensuring that interviews with the patients do not occur too closely to the childbirth weeks. The underlying assumption is that the period immediately following childbirth (ie, the first 2 months) may be a logistically and emotionally complex time for the family, with a particular focus on the mother’s availability and experience.

### Participant Recruitment and Withdrawal

The study’s target population includes all pregnant women residents in the PAT.

The inclusion criteria to participate in the study are as follows: (1) be pregnant; (2) be in a gestational state between the 24th and 26th week; (3) be aged ≥18 years; (4) have a smartphone with internet access, be able to download the app, and be able to use it; (5) be a resident of the PAT; and (6) know and understand the Italian language.

The exclusion criteria are as follows: (1) patients unable to provide informed consent, which is a prerequisite for participation in the study; (2) inadequate understanding of the Italian language; (3) substance addiction or in recovery for <1 year; (4) suicidal tendencies; (5) psychosis; (6) posttraumatic stress disorder; (7) depression or other psychiatric diagnoses; (8) social phobia; (9) women undergoing medically assisted procreation; and (10) positive obstetric history for late intrauterine fetal death and stillbirth, polyabortion, therapeutic abortion, or sudden infant death syndrome.

Recruited women who meet the inclusion criteria and give their consent to participate in the study will be enrolled in the research. All women who decide to take part in the study will be asked to sign an informed consent form at the time of enrollment after a careful explanation of the project; its aims; how the data will be collected, managed, and processed; the level of involvement required; and the duration of the research as well as any confidentiality issues. The woman will also be informed of the possibility of quitting the study at any time she wishes without any explanation and that this option would not impact the quality of care or interfere with her course of treatment.

The participant must provide informed consent freely, voluntarily, and in writing.

Participants will also receive a privacy policy statement regarding the data processing of their personal data during the research. They should provide their explicit consent to the data processing.

Copies of the study’s informed consent form and privacy consent form will be provided to the participant. This information will also be available in a dedicated section of the app.

A flowchart of the research project procedure in sown in the Figure 2.

**Figure 2 figure2:**
[figure not shown]
Flowchart of the research project procedure.

### Sample Size

This research project is designed as a proof-of-concept study, where a small sample is sufficient to achieve the intended aims. It was calculated that if nonparametric statistics are conducted (assuming the distribution is not normal), the sample should consist of 24 pregnant women with Bonferroni correction (Cronbach α=.025). The sample size and power for nonparametric tests (Kruskal-Wallis test and Wilcoxon post hoc test) c according to Noether [18]. If parametric statistics are conducted (assuming the normal distribution), the sample must instead consist of 41 pregnant women with Bonferroni correction (α=.025). Thus, with a power level set at 0.80, a significance level of .025, and factoring in a 20% potential dropout rate, we estimated that recruiting 50 women would be necessary to conduct the study.

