#### Quantitative Analysis

Statistical data processing will be conducted using the software R (version 4.0.0; R Foundation for Statistical Computing), SPSS Statistics (IBM Corp), and Stata17 (StataCorp LLC).

Categorical variables will be summarized by absolute and percentage frequency distributions and quantitative variables of appropriate centrality and variability indexes.

Descriptive analyses will be calculated both for psychological variables (QoL, anxiety, stress, depression, distress, the impact of external events, mindfulness, positive and negative affect, and emotional regulation) and usability (UX) and user involvement (UE) variables. These analyses will be performed on the variables analyzed at the beginning, during, and at the end of the interaction with Maia.

The relationships between variables will be analyzed mainly through ad hoc statistical tests, such as the chi-square test, Fisher exact test, 2-tailed *t* test for paired data or Wilcoxon nonparametric tests, and the sign test (based on an assessment of compliance with assumptions), to understand the differences between the beginning and the end of the course in the same study sample with respect to the variables under investigation.

Furthermore, univariate logistic models or multinomial regression models will be presented. Finally, to consider possible confounding factors, multiple regression models will be proposed, where the effects of the explanatory variables on the outcome variables will be adjusted for possible confounders.

For each analysis, statistical significance will be set at a *P* value of ≤.05.

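### The nonparametric sample size of 24 is justified by an independent-groups test that does not fit one group measured twice, and no stated effect size links it to the parametric 41

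*Protocol article*

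**What the plan says.** The Sample Size section of the protocol article gives two requirements.

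- Nonparametric case: "the sample should consist of 24 pregnant women with Bonferroni correction (Cronbach α=.025").
- Parametric case: "If parametric statistics are conducted (assuming the normal distribution), the sample must instead consist of 41 pregnant women with Bonferroni correction (α=.025").

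The method behind the first is given as "The sample size and power for nonparametric tests (Kruskal-Wallis test and Wilcoxon post hoc test"), with a citation to Noether. The section then takes the two cases to a recruitment target of 50 "with a power level set at 0.80, a significance level of .025, and factoring in a 20% potential dropout rate". It names no effect size, standard deviation, sidedness or endpoint.

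The Quantitative Analysis section lists paired t, Wilcoxon and sign tests "to understand the differences between the beginning and the end of the course in the same study sample". On the threshold it says "For each analysis, statistical significance will be set at a" P value of .05 or less. The Limitations section states that there is no control group. The outcome sections and Table 1 give two time points per questionnaire: weeks 4 and 8 for the primary measures, weeks 1 and 8 for the secondary ones.

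**The concern.** Two things do not fit.

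1. **The test.** Kruskal-Wallis compares independent groups, and post hoc tests after it presuppose at least three. This study has one group seen twice per questionnaire, and Kruskal-Wallis is not among the tests that the analysis section names. The 24 is therefore credited to a method that the design cannot use.
2. **The two numbers.** When differences are near normal, a rank test needs slightly more subjects than the t test for the same effect. Here it is said to need about 40% fewer (1 − 24/41 = 0.41), and no effect size is given that would explain this.

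Questionnaire scores may well prompt the nonparametric route. A reader could then take the article to say that 24 completers are enough for 80% power. If dropout were heavy, a study that fell well short could be described as adequately powered.

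**Working it through.** **Inputs from the article.** Power 0.80; α=.025 for sample size (sidedness not stated); 20% dropout; 24, 41 and 50 women; P≤.05 in the analysis. **Assumption.** The effect size is not given, so it is back-solved from 41.

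**Step 1: reproduce 41.** For a paired t test (noncentral t), two-sided α=.025:
- the standardized change giving exactly 0.80 power with 41 women is d=0.497;
- at d=0.5, power is 0.805 with n=41 and 0.793 with n=40, so 41 is exactly the requirement.

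**Step 2: reproduce 50.**
- 41 × 1.2 = 49.2, rounded up to 50. This is how the target appears to have been reached.
- Dividing by the retained fraction gives 41/0.8 = 51.25, so 52.
- 50 × 0.8 = 40 completers, with paired-t power of about 0.79.

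**Step 3: the signed-rank requirement at the effect behind 41.**
- By efficiency under normality: 41/0.955 = 42.9, so 43.
- By Noether: n = (z₁₋α/₂ + z₀.₈₀)² / [3(p − 0.5)²]. Here (2.241 + 0.842)² = 9.505 and p = Φ(√2 × 0.5) = 0.760, so n = 9.505/(3 × 0.260²) = 46.8, or 47.
- Neither route gives 24.

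**Step 4: the effect that would give 24.**
- p = 0.5 + √(9.505/(3 × 24)) = 0.863, which under normality is d of about 0.77. The paired t test would then need only 19 women.
- Noether's sign-test formula, with 4 in place of 3, gives p=0.815 and d of about 0.90, further from 0.5.
- Sidedness does not rescue it: at one-sided .025, 41 implies d=0.448 and 24 implies d=0.675.

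**Step 5: power of 24 women, by simulation.** For 24 to do the work of 41, the rank test needs a relative efficiency of 41/24 = 1.71. Each row uses one common shift for both tests, two-sided α=.025.

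| Distribution of differences | Signed-rank, n=24 | Paired t, n=41 |
|---|---|---|
| Normal | 0.50 | 0.81 |
| Laplace | 0.64 | 0.79 |
| t, 3 df | 0.72 | 0.80 |
| t, 2 df | 0.77 | 0.71 |

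Only the last, extremely heavy-tailed case favours 24. With 40 completers, d=0.5 and normal differences, signed-rank power is 77–78%.

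**Step 6: the two α levels.** At d=0.5 with 40 completers, paired-t power is about 0.79 at .025 and about 0.87 at .05. Any power statement therefore depends on which threshold is meant.

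**The case against.** The strongest reply is that the two figures are not shown to conflict. The article gives no effect size. Noether's measure is a probability, not a standardized mean difference, and the 24 is expressly conditional on non-normal data. The mismatch appears only after d=0.5 is inferred and converted under normality, and with t (2 df) differences 24 women on the rank test do outperform 41 on the t test. This stands to the extent that a reader who infers that the statement is impossible goes too far. The supportable claim is that the text does not reconcile the figures and that they imply different effects under ordinary distributions. Very heavy tails are unlikely for bounded scores.

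Second, recruitment does not rest on 24. That figure would need only 24/0.8 = 30 recruits, whereas 50 follows from 41. Ending with 24 of 50 women would take 52% dropout (26/50). The abstract calls the analysis mainly descriptive, and the Limitations section disclaims any evaluation of effectiveness. All of this stands, and it limits the harm to a misleading fallback figure.

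Third, a journal article may leave the effect size to the full protocol, and its list of tests is open-ended and includes Wilcoxon. That excuses brevity. It does not excuse naming an independent-groups test for a paired design, or calling a significance level Cronbach α.

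**Conclusion.** The statement is wrong as written and should be corrected. Kruskal-Wallis does not fit the design. The 24 is unsupported at the effect that reproduces 41: the signed-rank test needs about 43 to 47 women there, and 24 give about 50% power for normal and about 64% for Laplace differences. These sizes rest on the inferred d=0.5 at two-sided α=.025; at one-sided .025 the mismatch remains.

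Three minor points belong to the same correction: the Cronbach label, the inflation of 41 to 50 where division gives 52, and α of .025 in one section against .05 in the other.

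Two stronger readings are not supported.
- *That 50 recruits leave the study materially underpowered.* The shortfall is about one percentage point (0.79 against 0.80).
- *That the calculation serves only the secondary pre-post outcome.* The article names no endpoint. The primary outcome also includes a week 4 to week 8 difference, and a Bonferroni divisor of two (.05/2 = .025) would suit the two primary questionnaires as well. Only the sponsor can say which was meant.

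**What to change.** In the Sample Size section:

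1. Delete the 24 and the reference to Kruskal-Wallis with post hoc tests.
2. Replace Cronbach α with significance level.
3. State the endpoint, effect size and sidedness actually used. Do not assign the calculation to the secondary outcome unless the sponsor confirms it.
4. Use the same α here and in the Quantitative Analysis section.
5. Restate the power. If 0.5 was the assumed effect and .025 is kept, suitable wording is: *Fifty women recruited, about 40 evaluable after 20% dropout, give about 79% power (paired t test), or 77–78% (Wilcoxon signed-rank test, normal differences), for a standardized paired change of 0.5 at two-sided α=.025.* If another effect or α was used, recompute these figures.

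The cost is wording only, with no added participants. The stated power falls from 80% to about 79% if .025 is kept.
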